#### 2.8.2. Randomization

The equality of study arms will be achieved by a stratified, balanced (1:1) block randomization. Randomization will be stratified according to study site. The randomization will be undertaken independently at the Institute of Epidemiology and Medical Biometry, University of Ulm, using the randomization software ROM. Sealed envelopes are prepared for use in each study site, which contain the randomized group.

#### 2.8.3. Blinding

The study is single blinded, with the pathologists being blinded for the applied biopsy technique.

#### 2.8.4. Primary Endpoint Analysis

The primary endpoint is the detection of at least one molecular genetic alteration in NSCLC. Confirmatory and exploratory data analyses are performed for this dichotomous primary endpoint as follows: 

The difference in both groups based on the primary endpoint are evaluated using a Chi-square test (two sided at a significance level of 5%). All further analyses of the primary endpoint will be performed in an exploratory fashion. All results from these analyses will be regarded as hypothesis-generating, and not as proof of efficacy. Univariate and multiple logistic regression models to adjust for strata (study site) and potential confounding variables will be performed.

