#### 2.5.2. Randomization

Patients are randomized to either FB or CB for tissue sampling by a stratified, balanced (1:1) block randomization, stratified by study site. The randomization will be prepared at the Institute of Epidemiology and Medical Biometry, University of Ulm. Sealed envelopes will be prepared for use in every study site, containing the randomized group. The opening of an envelope has to be documented in detail on the case report form (CRF). Liquid biopsy is performed in every patient included in the study, and TBNA is performed if indicated, depending on local investigators’ decision, irrespective of randomization.

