#### 2.5.3. Liquid Biopsy Procedure

Prior to any bronchoscopic intervention, blood is drawn for liquid biopsy analysis.

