#### 2.8.1. Sample Size Estimate

Sample size calculation is based on the comparison of the detection rates for both techniques (FB and CB). Based on our earlier retrospective study, the cryobiopsy detection rate of EGFR was increased by approximately 50%, from 14% to 21% [40]. As our primary endpoint combines various aberrations, including PD-L1-expression level, a rate of detectable alterations of around 40% could be expected. With an expected relative increase of almost 50% for aberrations, related to a frequency of 40%, an absolute detection frequency of 55% was considered to be a conservative estimate.

The following assumptions were made for the sample size calculation: two-sided Chi-square test, type one error alpha = 0.05, power = 0.80. With a detection rate of 40% in the control FB group, and a conservative estimation of the detection rate of 55% in the experimental CB-group, and an assumption of equal number of patients in each group, 173 patients are required for each group, i.e., 2 × 173 = 346 patients in the whole trial.

Because of the short duration of observation in each patient, the rate of loss to follow up is very small. To allow a drop-out rate of up to 3% 10 extra patients need to be recruited, resulting in a total sample size of 356 patients. As seen in Figure 1, the sample size for recruitment has to be increased, because NSCLC is likely to form 80% of all tumors; about 45 will be small cell lung cancer (SCLC) and about 10% (25 cases) would not be diagnostic in each cohort. Therefore, 2 × 248 patients will be required for randomisation. Although there is no current data, it can be assumed that in some cases an endobronchial tumor will not be visible. As a rough estimate, we assume that in 8% of the cases (*n* = 44), it will not be possible to take a biopsy from the central airways. This therefore determines that the total number of recruited suspected lung cancer patients is 540.

Sample size calculation was performed by nQuery Advanced 8.1.

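### The confirmatory chi-square leaves out the randomisation stratum (site) and the pre-bronchoscopy liquid-biopsy result: a valid, correctly powered test that forgoes an efficiency gain of unknown size

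*Protocol article*

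**What the plan says.** **Endpoint and test.** Section 2.8.4 defines a binary endpoint: "The primary endpoint is the detection of at least one molecular genetic alteration in NSCLC". The arms are compared with an unadjusted two-sided chi-square test at 5%. The section then says: "All further analyses of the primary endpoint will be performed in an exploratory fashion", and calls the results of those analyses hypothesis-generating. Adjusted models fall in that second group: "Univariate and multiple logistic regression models to adjust for strata (study site) and potential confounding variables will be performed". Site is the only covariate named.

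**Design.** Sections 2.5.2 and 2.8.2 describe 1:1 block randomisation stratified by study site. On the blood sample, 2.5.2 states: "Liquid biopsy is performed in every patient included in the study", irrespective of arm. Section 2.5.3 gives its timing: "Prior to any bronchoscopic intervention, blood is drawn for liquid biopsy analysis". Section 2.6.2 includes the blood samples in the molecular genetic testing. Section 2.8.5 uses the result only for secondary questions of diagnostic value.

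**Sample size.** Section 2.8.1 assumes a "two-sided Chi-square test, type one error alpha = 0.05, power = 0.80", with 40% detection under forceps biopsy and 55% under cryobiopsy. This gives 173 evaluable patients per arm.

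**The concern.** An alteration is detected in tissue only if the tumour carries one and the technique finds it. The trial asks about the second step; the first adds noise. A blood sample drawn before the biopsy cannot be altered by the assigned technique and carries some information about the first step. Leaving it out of the confirmatory test gives up precision that costs no further data.

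Site raises the same issue. It is a randomisation stratum, and 2.6.2 describes different sequencing platforms and fusion or copy-number methods at different sites, so detection rates may plausibly differ between them. A test that ignores a stratum related to the outcome tends to be slightly conservative.

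This is more than detail left to the SAP. As 2.8.4 is worded, only the unadjusted chi-square is confirmatory, so a SAP that made an adjusted analysis confirmatory would depart from the published text.

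**Working it through.** **1. The plan's own figure.** Inputs from 2.8.1: rates 0.40 and 0.55 (mean 0.475), two-sided 5%, 80% power.

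n = [1.960·√(2·0.475·0.525) + 0.842·√(0.40·0.60 + 0.55·0.45)]² / 0.15² = [1.384 + 0.588]² / 0.0225 ≈ 172.8, rounded up to 173 per arm.

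Power at 173 per arm is 0.800. The sample size is right for the planned test.

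**2. How much noise comes from tumour biology.** The article gives no prevalence of alterations. Assume 70% and no tissue false positives. Technique sensitivities are then 0.40/0.70 = 0.571 and 0.55/0.70 = 0.786.

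- Variance of the risk difference: (0.24 + 0.2475)/173 = 0.00282.
- Part due to which tumours carry an alteration: (0.571² + 0.786²)·0.70·0.30/173 = 0.00115, or 41%. Its SD is 3.4 points, against a planned effect of 15.
- At assumed prevalences of 60% and 80% the share is 63% and 24%.

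This caps what a perfect marker of alteration status could remove. The test already allows for this variation.

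**3. What an imperfect marker removes.** If φ is the within-arm correlation of liquid result and tissue detection, the residual variance is about (1 − φ²) of the total. The sample size for 80% power becomes about 173·(1 − φ²).

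| φ (assumed) | Power at 173 per arm | n per arm for 80% power |
|---|---|---|
| 0.2 | 0.816 | 167 |
| 0.3 | 0.836 | 158 |
| 0.4 | 0.864 | 146 |
| 0.5 | 0.900 | 130 |
| 0.6 | 0.939 | 111 |

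One case in full: prevalence 0.70, liquid sensitivity 0.60, specificity 0.95.

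- P(liquid positive) = 0.42 + 0.015 = 0.435.
- Tissue detection given liquid positive versus negative: 0.55 versus 0.28 (forceps), 0.76 versus 0.39 (cryobiopsy).
- φ² averaged over arms = 0.105, so n = 173·0.895 ≈ 155.

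**4. Simulation.** 173 per arm, 40% versus 55%, unadjusted chi-square against a Mantel-Haenszel test stratified on liquid status, 20,000 trials per scenario. Liquid and tissue results are independent given true alteration status.

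| Prevalence | Liquid sensitivity / specificity | Chi-square | Stratified |
|---|---|---|---|
| 0.6 | 0.8 / 0.95 | 0.785 | 0.933 |
| 0.6 | 0.5 / 0.80 | 0.792 | 0.823 |
| 0.7 | 0.6 / 0.95 | 0.794 | 0.840 |
| 0.7 | 0.7 / 0.95 | 0.788 | 0.853 |
| 0.8 | 0.8 / 0.95 | 0.793 | 0.839 |
| 0.8 | 0.5 / 0.80 | 0.793 | 0.806 |

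Simulated type I error is 0.046 to 0.053 for the stratified test and 0.043 to 0.050 for the chi-square. Part of the smallest gains therefore only reflects the chi-square running slightly below its nominal level.

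**5. Weaker link.** Section 2.8.1 counts PD-L1 expression in the endpoint, while 2.6.1 describes it only for tissue and TBNA material. Assume that 40% of positives are invisible to blood, that the liquid false-positive rate is 10%, and that liquid sensitivity is 40 to 80% for the rest. The gain over prevalences of 60 to 80% is then about 1 to 6 points. No scenario loses power.

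The simulations stratify on liquid status only. The article gives nothing from which the gain from site could be sized.

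**The case against.** The strongest reply is that nothing here is wrong. The chi-square is valid under randomisation and is the test the sample size was computed for; preferring a more efficient test is a choice. That stands, and it limits the point to an efficiency suggestion.

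Three stronger readings are tempting, and the article does not support them.

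- **That liquid biopsy is a strong predictor.** No concordance or sensitivity figure is given. Its diagnostic value is itself a study question (2.3, 2.8.5), and the Background calls the clinical relevance of blood-based characterisation unclear. The largest gains need low prevalence, high liquid sensitivity and few false positives. At 60% prevalence they also imply that cryobiopsy finds 0.55/0.60 = 92% of all alterations.
- **That chance imbalance biases the primary result.** It is random error covered by the 5% level. The Discussion lists possible imbalance in patient characteristics, tumour growth or stage, not in alteration prevalence, and expects the sample size to give good balance.
- **That the liquid result is wholly pre-biopsy.** Only the blood draw is stated to come first. Section 2.8.3 blinds pathologists to technique, and the article does not say that blood is called without knowledge of the tissue result.

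It can also be said that the exploratory models may include liquid status as a potential confounder. They may, but 2.8.4 keeps them out of the confirmatory analysis.

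**Conclusion.** The point holds as a modest improvement. The confirmatory test omits the randomisation stratum and a likely predictive measurement taken from blood drawn in every included patient before bronchoscopy. The planned test is valid and correctly powered at 173 per arm.

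The gain from liquid status is unknown. Under assumed prevalence of 60 to 80% it runs from about 1 point of power to about 15. With prevalence 0.70, liquid sensitivity 0.6 to 0.7 and specificity 0.95, power is about 0.84 to 0.85; a PD-L1 component invisible to blood would lower that. Prevalence, liquid accuracy, the PD-L1 share and conditional independence are all assumptions. The direction is more secure than the size: no scenario lost power, and type I error stayed near 5%.

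**What to change.** Before unblinding, amend 2.8.4 and carry the change into the SAP:

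- **Confirmatory analysis:** a Mantel-Haenszel test stratified by site and liquid-biopsy status (detected / not detected / missing), or logistic regression with arm, site and liquid status, reporting a standardised risk difference with CI. With five sites and three categories there are at most 15 strata, on average 346/15 ≈ 23 patients each.
- **Condition:** use liquid status only if it is called without knowledge of arm and of the tissue result. If that cannot be assured, stratify by site alone.
- **Sensitivity analysis:** keep the unadjusted chi-square.
- **Sample size:** leave it unchanged, because the liquid-tissue correlation is unknown.

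No extra data are needed. The cost is an amendment to the primary-analysis wording while the trial is recruiting, and a rule for independent calling of the blood result. If regression is chosen, the conditional odds ratio must also be standardised to a risk difference.

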#### 2.8.5. Secondary Endpoint Analysis

The secondary, exploratory objectives and safety data are analysed by statistical methods for comparison of two unpaired groups, as appropriate for the characteristic of the variables, e.g., chi-square test for categorical and *t*-test/Mann–Whitney U test for continuous variables. The assessment of the diagnostic value of liquid biopsy and TBNA, as both single techniques and in combination, will be undertaken by logistic regression analysis and ROC analysis. In order to investigate effects of subgroups and putative confounding factors, further analyses are performed, using generalized linear regression models as appropriate.

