### 2.3. Study Objectives

The primary objective is to assess differences in detection of molecular genetic alterations in NSCLC between FB and CB (Figure 2).

The secondary objectives assess differences in the detection of molecular genetic alterations in NSCLC between liquid biopsy, solid tumor tissue biopsy obtained by bronchoscopic techniques, cytological material obtained by TBNA, and to compare combined methods (tissue biopsy, TBNA and liquid biopsy) with single techniques, to evaluate differences between naïve and processed tumor tissue specimens (e.g., by microdissection), and finally, to assess differences in side effects (e.g., peri-interventional bleeding). 

The exploratory objectives analyze tumor mutational burden with regard to solid tumor tissue by FB or CB and cytologic material by TBNA and liquid biopsy.

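### Secondary comparisons of liquid biopsy, TBNA, tissue and their combinations are made within patients, but the plan assigns them to tests for unpaired groups and names no paired method

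*Protocol article*

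**What the plan says.** Section 2.3 sets secondary objectives that compare detection between liquid biopsy, bronchoscopic tissue and TBNA cytology. It also aims "to compare combined methods (tissue biopsy, TBNA and liquid biopsy) with single techniques". Further aims there are naïve against processed tissue specimens, and side effects.

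Section 2.5.2 fixes who contributes which specimen: "Liquid biopsy is performed in every patient included in the study, and TBNA is performed if indicated", in both cases irrespective of the randomized arm. Section 2.6.2 has each available specimen genotyped.

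For the analysis, section 2.8.5 opens: "The secondary, exploratory objectives and safety data are analysed by statistical methods for comparison of two unpaired groups". Its examples are the chi-square test for categorical variables and the t-test or Mann–Whitney U test for continuous ones. The next sentence assigns the diagnostic value of liquid biopsy and TBNA, singly and combined, to logistic regression and ROC analysis. The section closes with generalized linear models for subgroups and confounders. The article names no paired or clustered method.

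**The concern.** A test for two unpaired groups assumes that the two sets of results come from different people. That holds for FB against CB. It does not hold when one patient supplies both a tissue result and a liquid biopsy result, or both a TBNA result and a tissue result. All these specimens sample the same patient's disease, so positive correlation is to be expected, and an unpaired test ignores it.

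Combined against single is a special case. The combination is positive whenever the single technique is, so patients can only be gained and never lost. An unpaired test treats this nested gain as if it came from two independent samples.

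At stake is the question that the Discussion says the trial will answer: which single technique or combination characterizes the tumor best. An analysis run as worded could report no demonstrable added yield where the paired data show one.

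**Working it through.** **The plan's own figure.** Section 2.8.1 gives "two-sided Chi-square test, type one error alpha = 0.05, power = 0.80", then "With a detection rate of 40% in the control FB group" and "a conservative estimation of the detection rate of 55% in the experimental CB-group". With pooled rate 0.475:

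n = [1.96·√(2·0.475·0.525) + 0.842·√(0.40·0.60 + 0.55·0.45)]² / 0.15² = 172.8, so 173 per group.

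This reproduces "173 patients are required for each group, i.e., 2 × 173 = 346 patients in the whole trial". The primary comparison is between arms, so the pairing problem does not touch it.

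**Inputs for the secondary comparisons**
- Patients with both tissue and liquid biopsy: 356 over both arms (section 2.8.1: "To allow a drop-out rate of up to 3% 10 extra patients need to be recruited, resulting in a total sample size of 356 patients"), or 178 within one arm.
- Detection rates: not given for liquid biopsy. Assumed 55% against 45%.
- Within-patient correlation φ: not given. Assumed 0.3 to 0.7, with 0 as reference.

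**Standard error of the difference.** Here p₁q₁ = p₂q₂ = 0.2475.
- Unpaired: √[(p₁q₁ + p₂q₂)/N] = √(0.495/N)
- Paired: √[(p₁q₁ + p₂q₂ − 2φ√(p₁q₁p₂q₂))/N] = √[0.495(1−φ)/N]
- Ratio: 1/√(1−φ)

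**True size of the nominal 5% unpaired test** (equal rates): 2[1 − Φ(1.96/√(1−φ))].

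| φ | SE ratio | True size |
|---|---|---|
| 0 | 1.00 | 5.0% |
| 0.3 | 1.20 | 1.9% |
| 0.5 | 1.41 | 0.6% |
| 0.7 | 1.83 | 0.035% |

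Neither column depends on N. Simulated paired tables agree (0.03% to 0.04% at φ = 0.7), and McNemar's test stays near 5% throughout.

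**Power for 55% against 45%.** Unpaired: Φ[(0.10 − 1.96·SE_unpaired)/SE_paired]. Paired: Φ[0.10/SE_paired − 1.96].

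- N = 356, φ = 0.3: SEs 0.0373 and 0.0312. Unpaired Φ(0.86) = 81% (79% simulated); paired Φ(1.25) = 89%.
- N = 356, φ = 0.5: SEs 0.0373 and 0.0264. Unpaired Φ(1.02) = 85% (83% simulated); paired Φ(1.83) = 97%.
- N = 178, φ = 0.3: SEs 0.0527 and 0.0441. Unpaired 47%; paired 62%.
- N = 178, φ = 0.5: SEs 0.0527 and 0.0373. Unpaired 46%; paired 76%.

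Formula and simulation differ by about one point, so the unpaired figures for 356 patients are best read as about 80% and 84%.

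**Nested comparison.** These counts are illustrative; no assumed correlation is needed.
- 89 of 178 by tissue, 98 of 178 combined (9 gained, 0 lost): chi-square p = 0.34; exact paired p = 2·0.5⁹ = 0.004.
- 169 of 356 against 179 of 356 (10 gained, 0 lost): chi-square p = 0.45; exact paired p = 2·0.5¹⁰ = 0.002.

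Since losses are impossible here, the informative quantity is the proportion gained. In the second example this is 10/356 = 2.8%, exact 95% CI 1.4% to 5.1%.

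**The case against.** The strongest reply is that section 2.8.5 should be read as two rules. The general opening sentence would cover FB against CB contrasts, such as side effects and combined detection by arm. The specific next sentence would give liquid biopsy and TBNA their own methods. If each patient's tissue result were the outcome and the liquid or TBNA result a predictor, there would be one row per patient and the within-patient link would be used. This reading is possible, so a reader should not infer that chi-square and Mann–Whitney tests are certainly the only plan for these comparisons. But the sentence does not state the model form. Ordinary logistic regression on stacked specimens would repeat the independence error, and the opening sentence still covers the secondary objectives without exception. Its flexible wording allows a choice by type of variable, within unpaired methods.

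A second reply is that a SAP is announced before any analysis and may settle this. That is so, but the point is not missing detail: the article names a class of test that does not suit these objectives, and a SAP that follows it inherits the problem.

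Two stronger readings lack support in the text:
- A reader might infer that TBNA patients would be compared with all patients, mixing technique with selection. The article does not state the analysis set for TBNA.
- A reader might take naïve against processed tissue to be within-patient. Section 2.3 does not say that both come from the same patient.

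**Conclusion.** The point holds at moderate severity. As worded, section 2.8.5 puts within-patient comparisons under unpaired tests, and nothing in the article supplies the pairing. Under positive correlation the consequence is conservative: intervals too wide, p-values too large, power lost. A reader might infer inflated false positives, but that would require negative correlation. At zero correlation the two analyses agree.

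The SE ratio and true size depend only on the assumed correlation. The power figures rest also on assumed rates of 55% and 45% and on the number of patients. The low power for 178 patients might be read as the general result, but it applies only to an analysis within one arm. Liquid biopsy is taken in both arms, and with all 356 evaluable patients the loss is about 9 points at correlation 0.3 and 13 at 0.5.

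A reader might also see a threat to the trial's main conclusion. There is none: the affected analyses are exploratory, and the primary FB against CB test and its sample size stand.

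**What to change.** - Limit the unpaired tests to FB against CB contrasts, including side effects and combined detection by arm.
- For liquid biopsy against tissue and TBNA against tissue, use McNemar's test with a confidence interval for the paired difference, in patients who have both specimens. Alternatively, use a GEE or mixed logistic model with patient as the cluster.
- Use paired methods when ROC curves from the same patients are compared.
- For combined against single, report the proportion of patients gained with an exact confidence interval.
- Apply the paired methods to naïve against processed tissue only if both come from the same patient.

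The cost is wording in the analysis plan and standard procedures. Results are already generated for each specimen in each patient, so no new data, patients or change of sample size are needed.

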### 2.9. Trial Oversight and Ethics Approval

All procedures including FB, CB, TBNA and blood extraction for liquid biopsy are standardized routine and approved techniques using CE certified medical devices for diagnosis of lung cancer. The diagnostic workflow and its results are analyzed in this study setting, but they will not be altered at all, so all diagnostic procedures are performed as in routine clinical practice. This study protocol follows the German Medical Association Professional Code with institutional review board (IRB)-approval of the local IRB for each investigational site.

This clinical study is conducted in accordance with all appropriate laws and regulations, including, but not limited to, the Guideline for Good Clinical Practice (GCP), the Code of Federal Regulations (CFR), Directive 2001/20/EC, and the ethical principles of the Declaration of Helsinki and its amendments. Nothing in this document limits the authority of a physician to provide emergency medical care as appropriate.

This study was approved by the leading ethics committee at the University hospital of Tuebingen (644/2018BO1) between 29 August 2018 and 12 December 2018, and approved by local ethics committees at all participating study sites.

